## **Assessment Procedure**

This trial will include two experienced treatment-blind assessors at each site, who will independently administer the mentioned outcome measures at baseline and at 2, 4, 8, 12, and 24 weeks. The research coordinator at each site will advise and remind patients at each visit about non-disclosure of their treatment groups to the assessor.

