## **Contents**

### **1. Specific Aims and Hypotheses**

### **2. Outcomes**

### **3. Statistical Methods**

#### **3.1. Interim Analyses**

#### **3.2. Statistical Analyses**

### **1. Specific Aims and Hypotheses**

The aim of this trial is to determine the efficacy and safety of MBC in patients with MDD in comparison with standard care in Pakistan. To reduce the variance found in treatment-as-usual and isolate the impact of MBC, this trial will limit medication choices to either paroxetine or mirtazapine (as per previously published trials). We hypothesize that, compared to standard care group, the MBC group will have significantly higher rates and shorter times to response and remission, along with lower rates of dropout and side effect burden.

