### **2. Outcomes**

A form will be designed to collect sociodemographic and clinical characteristics from the medical records, and this information will be confirmed in a clinical interview. HDRS scores will be used to inform two primary outcomes measures: estimated time from randomization to response (defining response as  $\geq 50\%$  reduction in HDRS from baseline) and remission (defined as HDRS score  $\leq 7$ ) (Hamilton, 1960).

Secondary outcome measures will include changes in severity of depressive symptoms (HDRS score). An additional checklist with six common side effects (dry mouth, diarrhea or constipation, dizziness or drowsiness, loss of appetite or nausea, headache, and excessive sweating); and the FISBER, will be used to measure side effects at each treatment visit. The pill count method will be used to measure treatment adherence.

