### 3.2. Statistical Analyses

A treatment-blind statistician will analyze the data after completion of follow-ups for all recruited participants using SPSS for Windows, version 20.0 (IBMCorp., Armonk, N.Y.).

Like the Guo et al. (2015) trial, we will use independent-sample t-tests, Mann-Whitney U tests, and chi-square tests, to compare sociodemographic and clinical characteristics, discontinuation, response and remission rates, and side effects as appropriate. Full intent-to-treat analyses will be carried out to determine all-cause discontinuation. Estimated time from randomization to response and remission will be calculated using Kaplan-Meier survival analyses, and a comparative analysis will be facilitated using the Cox proportional hazards regression model. Analysis of covariance will be used to compare the changes in HDRS scores between the two groups. Additional subgroup analysis might be carried out to understand group-differences due to age, gender, duration of illness, and number of previous episodes. The significance threshold will be  $p < 0.05$  (two-tailed) for all analyses.

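### The side-effect checklist is compared between arms with no treatment-emergent or attribution rule, so earlier remission under MBC can appear as fewer side effects or hide a real excess

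*Combined protocol and SAP*

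**What the plan says.** SAP section 1 expects the MBC arm to do better on response and remission, "along with lower rates of dropout and side effect burden". Section 2 names two side-effect instruments. One is a checklist of "six common side effects (dry mouth, diarrhea or constipation, dizziness or drowsiness, loss of appetite or nausea, headache, and excessive sweating". The other is FIBSER, which the protocol (Measurement-based Care) describes as a patient report of antidepressant side effects. Both "will be used to measure side effects at each treatment visit".

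For analysis, section 3.2 plans t-tests, Mann-Whitney tests and chi-square tests "to compare sociodemographic and clinical characteristics, discontinuation, response and remission rates, and side effects as appropriate". It gives no time point, per-patient summary, treatment-emergent definition or attribution rule for side effects. The only analysis of change in the SAP is for depression severity: "Analysis of covariance will be used to compare the changes in HDRS scores between the two groups".

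The protocol (Assessment Procedure) has two blinded assessors per site "who will independently administer the mentioned outcome measures at baseline and at 2, 4, 8, 12, and 24 weeks". This may or may not include the checklist, because the outcome sections tie the checklist to treatment visits.

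**The concern.** Appetite loss, drowsiness or headache can come from depression as well as from an antidepressant. That is general clinical knowledge. The documents mention physical symptoms of the illness only in general terms and do not link them to the six items. Randomisation balances such symptoms at the start but not afterwards.

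The trial expects remission to come sooner under MBC. If it does, illness symptoms on the checklist clear sooner in that arm, and a raw comparison can read this as better tolerability. A success on the primary outcome would then partly produce the safety result.

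The opposite error is also possible. The protocol's Introduction reports higher antidepressant doses under MBC in the replicated trial. A real drug-related excess could be cancelled by the faster clearing of illness symptoms. At stake is a named hypothesis on a secondary outcome.

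**Working it through.** The plan gives no figure for side effects, so there is none to reproduce.

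**Inputs from the documents.** Remission in the replicated trial was 73.8% under MBC and 28.8% under standard care (protocol, Introduction), a difference of 0.45. The planned 120 participants at 1:1 give 60 per arm. Tests are two-sided at 0.05.

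**Assumptions, not in the documents.** For steps 1 and 2, an item is present from illness in a share *n* of non-remitters (30–50%) and *r* of remitters (10–20%), with no drug effect in either arm. The remission rates *R* are taken to apply at week 24.

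**Step 1: prevalence at the end of the trial.** Prevalence = R·r + (1 − R)·n, so MBC minus standard care = −0.45·(n − r).
- With n = 40% and r = 10%: MBC 0.738×0.10 + 0.262×0.40 = 0.179; standard care 0.288×0.10 + 0.712×0.40 = 0.314; difference −13.5 points.
- Smallest gap (30% − 20%): 0.45×0.10 = 4.5 points. Largest gap (50% − 10%): 0.45×0.40 = 18 points. Both favour MBC.

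**Step 2: week 2, approximating an ever-reported summary.** A symptom that persists from before treatment is counted at the first on-treatment visit, when few patients have remitted. Assuming a constant remission hazard, R(2) = 1 − (1 − R)^(2/24).
- MBC: 1 − 0.262^(1/12) = 0.106. Standard care: 1 − 0.712^(1/12) = 0.028. Difference 0.078.
- Multiplied by gaps of 0.10, 0.30 and 0.40, this gives 0.8, 2.3 and 3.1 points.

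**Step 3: which analysis removes the artefact.** Now assume that illness causes the item at baseline in a share π of both arms, that it clears on remission, and that the drug causes it in 20% of both arms. The true drug difference is zero. Prevalence = 1 − (1 − 0.20)(1 − π(1 − R)), and the difference is 0.80×0.45×π = 0.36π. For π from 10% to 60% this is 3.6 to 21.6 points. Simulating 4,000 trials of 60 per arm at π = 40% gives:

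| Analysis | MBC minus standard care (points) | Trials with p < 0.05 |
|---|---|---|
| Raw occurrence | −14.4 | 38% |
| Change from baseline | −14.3 | 31% |
| Baseline as covariate | −14.3 | 43% |
| Items absent at baseline, present later | +0.2 | 5% |

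Baseline is already balanced by randomisation. Adjusting for it therefore leaves a difference that arises afterwards.

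**Step 4: the opposing force.** With π = 40% and a drug-caused rate of 20% under standard care, the raw difference is zero when (1 − d)(1 − 0.40×0.262) = 0.80×(1 − 0.40×0.712). This gives 1 − d = 0.572/0.895 = 0.639, so d is about 36% under MBC. A real excess of 16 points would appear as no difference. At d = 30% the raw comparison averages −5.4 points and the treatment-emergent one +10.3 (truth +10). At d = 40% they average +3.4 and +20.1 (truth +20).

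**Step 5: washout.** The one-week washout precedes assignment. A symptom present in 30% of both arms that does not clear with remission gave a difference of 0.0 and p < 0.05 in 5% of simulated trials.

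**The case against.** Several points on the other side stand.

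- **Size.** The 4.5–18 point range fits only end-of-trial point prevalence. The plan does not name a summary, and an ever-reported one brings the figure down to about 1–3 points. The prevalences are assumed, and setting non-remitters above remitters fixes the sign.
- **Direction.** A reader might infer that MBC is bound to look better tolerated. The documents do not support this: higher doses under MBC push the other way and could cancel or reverse the effect. Cancellation is, however, the masking problem itself.
- **Format.** Scoring and wording of the checklist are not given, so it may be graded or may ask about attribution. This silence calls for a statement in the SAP; it does not show that the comparison is sound.
- **Baseline.** The Assessment Procedure may already provide a baseline checklist. If so, only the analysis text has to change.
- **Weight.** This is one of two instruments for a secondary outcome in a trial that calls itself exploratory. FIBSER rates burden directly and asks about the antidepressant. That limits the damage but does not repair the checklist comparison.

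Two further inferences are tempting and wrong. Washout symptoms do not bias the comparison, because washout comes before 1:1 randomisation; they add noise. The absence of a baseline covariate is not the cause either, and adding one, or using change scores, would fix nothing (step 3).

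**Conclusion.** The concern holds as a possible bias in one secondary comparison. Neither its direction nor its size is certain. Under the stated prevalences it is about 4.5–18 points in favour of MBC for end-of-trial prevalence and about 1–3 points at week 2, before any dose effect. It rests on three assumptions: that some checklist items reflect illness, that these clear with remission, and that remission differs between arms about as in the replicated trial.

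The missing element is a treatment-emergent rule. In the simulation that rule brought the spurious difference to about zero and recovered real drug differences. The simulation let illness symptoms be present at baseline or not at all, so illness symptoms that first appear later would still be counted. The time-to-response and time-to-remission analyses are unaffected.

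**What to change.** - State that the checklist is among the outcome measures taken at the baseline in the Assessment Procedure, after washout and before the first dose.
- In SAP section 3.2, base the between-arm comparison on treatment-emergent items: absent at baseline and present later, or worse than baseline if graded. Name the time point and the per-patient summary.
- Show raw occurrence descriptively, alongside antidepressant dose by arm.
- Leave FIBSER unchanged.
- If no baseline checklist was collected, report the raw comparison with an explicit caveat and do not use it to support the lower-burden hypothesis. This may be the position already: SAP section 3.1 speaks of interim analyses in the past tense, which suggests that the trial was well advanced.

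The cost is at most six questions at a visit already planned and a few lines of SAP text. If the baseline checklist exists, only the text changes. The downside is that a drug effect that only prolongs a pre-existing symptom is not counted.

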### **Study Intervention and Procedure**

After providing informed consent, eligible patients will enter a one-week washout phase to eliminate any effects of psychotropic medications previously taken. After washout week, the patients will be assigned to treatment arms based on randomization schedule, where they will receive either **open-label paroxetine**

(10–50mg/day) or open-label mirtazapine (7.5–45mg/day). All patients will be followed for 24-weeks after randomization. This dosage range is recommended by the US Food and Drug Authority (*Paxil - Highlights of Prescribing Medication*, 2022; *Remeron -Highlights of Prescribing Medication*, 2022). Paroxetine is a commonly prescribed antidepressant, working as a selective serotonin reuptake inhibitor, while Mirtazapine, which works as an alpha-2 antagonist, has a different mechanism of action. Similar to the Guo et. al study (Guo et al., 2015), the decision about the prescription of drug and dosage will be made by the treating psychiatrists/GP. Depending on the duration of prescribed dosage, symptoms and side effects, the psychiatrist/GP will make adjustments. In case of intolerability or inefficacy, one medication change between paroxetine and mirtazapine will be allowed. Short-acting benzodiazepines, prescribed occasionally for agitation, anxiety, and insomnia, will be permitted, as well as any other medications not affecting the CNS.

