### ***Measurement-based Care***

At every outpatient visit, patient’s feedback will be recorded through the 16-item Quick Inventory of Depressive Symptomatology–Self-Report (QIDS-SR) (Rush et al., 2003) and the Frequency, Intensity, and Burden of Side Effects Rating scale (FIBSER) (Wisniewski et al., 2006). The QIDS-SR is used to measure depressive symptoms in the past one week, with higher scores indicating higher severity (Rush et al., 2003). FIBSER is completed by the patient to report antidepressant side effects on the domains of frequency, intensity, and burden (Wisniewski et al., 2006). A total score >4 is indicative of current treatment being unsuitable and requires revision to dosage/medication (Trivedi, 2009).

The patient’s responses on these self-report measures will inform and guide physician’s decisions. Following a stepwise approach, the treatment schedule will outline the dosage adjustment, and medication changes needed to mitigate the side effects, and promote therapeutic benefit for each patient. Originally driven from the STAR\*D project ([www.star-d.org](http://www.star-d.org)), the treatment schedule used by the Guo et. al. (2015) study (Guo et al., 2015) will facilitate the treatment schedule (Table 1), for this study. However, the starting dosage has been modified following a discussion with the stakeholders, which highlighted patient preference for slower dose titration when initiating preference. Treating physicians will undergo a two-day training to get acquainted with use of MBC schedule. Moreover, an independent research coordinator will be designated at each site to compare the physician’s clinical notes against the MBC treatment guidelines to ensure compliance and standardization. In case of any deviation from the MBC schedule, the physician will be notified and asked to make necessary treatment amendments.

*Table 1. The Measurement-Based Care Schedule*

| Time Point and Measure  | Clinical Status  | Treatment Plan                                                         |                                                                       |
|-------------------------|------------------|------------------------------------------------------------------------|-----------------------------------------------------------------------|
|                         |                  | Paroxetine                                                             | Mirtazapine                                                           |

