## **Outcome measures**

A form will be designed to collect sociodemographic and clinical characteristics from the medical records, and this information will be confirmed in a clinical interview. HDRS scores will be used to inform two primary outcomes measures: estimated time from randomization to response ( $\geq 50\%$  reduction from baseline) and remission (HDRS score  $\leq 7$ ) (Hamilton, 1960).

Secondary outcome measures will include: severity of depressive symptoms (HDRS score), severity of manic or hypomanic symptoms according to the (YMRS score) (Young et al., 1978). An additional checklist with six common side effects (dry mouth, diarrhea or constipation, dizziness or drowsiness, loss of appetite or nausea, headache, and excessive sweating), along with FISBER, will be used to measure side effects at each treatment visit. The pill count method will be used to measure treatment adherence.

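### Three of the six side-effect checklist items each join two symptoms, so differences between arms in the separate symptoms may be diluted or, at worst, cancelled; record nine single symptoms instead.

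*Combined protocol and SAP*

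**What the plan says.** The protocol (Outcome measures) and the SAP (2. Outcomes) describe the same form: "An additional checklist with six common side effects", namely "dry mouth, diarrhea or constipation, dizziness or drowsiness, loss of appetite or nausea, headache, and excessive sweating". The SAP adds a second instrument, "and the FISBER, will be used to measure side effects at each treatment visit", which is evidently FIBSER with two letters transposed. The protocol section Measurement-based Care describes it: "FIBSER is completed by the patient to report antidepressant side effects on the domains of frequency, intensity, and burden".

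SAP 1 hypothesises better response and remission under measurement-based care (MBC), "along with lower rates of dropout and side effect burden". SAP 3.2 provides t-tests, Mann-Whitney U tests and chi-square tests to compare, among other things, "discontinuation, response and remission rates, and side effects as appropriate". It also says: "Full intent-to-treat analyses will be carried out to determine all-cause discontinuation".

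Neither document states how a checklist item is graded, whether the two halves of a joined item are captured separately, or how the checklist is summarised over visits or patients.

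**The concern.** Both documents count the list as six side effects, so the natural reading is one response per item. On that reading, a patient with diarrhea and a patient with constipation get the same entry.

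This matters more here than in a trial of one fixed drug, because changing drug is part of how the MBC schedule deals with side effects. Table 1 has ten rows for intolerable side effects. Eight call for a switch outright in both drug columns, and the other two (the partial-response rows at weeks 4 and 6) offer one. The protocol says that mirtazapine "has a different mechanism of action" from paroxetine. It also reports more treatment adjustments under MBC in the trial being replicated (44 against 23). The arms could therefore differ in drug exposure, and with it in the mix of symptoms.

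The checklist is the only named instrument that identifies individual side effects. If two joined symptoms move in opposite directions, the item shows less difference than either symptom does. At stake is the symptom-level part of the safety aim. The primary outcomes are not affected.

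**Working it through.** **Count.** Single items: dry mouth, headache, excessive sweating (3). Joined items: diarrhea/constipation, dizziness/drowsiness, loss of appetite/nausea (3). Only the first joined pair consists of opposites. Separate symptoms: 3 + 2 × 3 = 9.

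**Inputs from the documents.** 120 participants (Sample size) allocated 1:1 (Randomization and masking), so 60 per arm; two-sided 0.05 (SAP 3.2). The plan gives no power figure for side effects, so there is none to reproduce.

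**Assumed inputs.** The documents give no symptom rates. For illustration:
- standard care: first symptom 25%, second symptom 5%;
- MBC: first symptom 10%;
- the two symptoms do not occur together;
- each item is scored present or absent.

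**Formula.** Let *s* be the share of the fall in the first symptom that reappears as its partner. The fall is 25% − 10% = 15 points, so:
- second symptom under MBC = 5% + *s* × 15%;
- joint item under MBC = 10% + 5% + *s* × 15% = 15% + *s* × 15%;
- joint item under standard care = 25% + 5% = 30%.

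Power is the exact probability that the uncorrected two-sided chi-square test rejects, summed over all pairs of binomial counts with 60 per arm.

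| Share traded | Joint item, standard care | Joint item, MBC | Difference (points) | Power |
|---|---|---|---|---|
| 0 | 30% | 15% | 15 | 51% |
| 1/4 | 30% | 18.75% | 11.25 | 31% |
| 1/2 | 30% | 22.5% | 7.5 | 16% |
| 3/4 | 30% | 26.25% | 3.75 | 8% |
| 1 | 30% | 30% | 0 | 5% |

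**Comparison with separate recording.** The first symptom alone, 25% against 10%, gives 58% (0.585) whatever the share traded. At a full trade the second symptom is 5% against 20%, which gives 73%.

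**Reading.** With no trade, joining costs little (51% against 58%). The loss grows with the share traded, and the item shows no difference only at a full trade. In this example a full trade means that 0.15 × 60 = 9 MBC patients, net of standard care, lose one symptom and gain the other.

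**The case against.** A reader might infer that the safety comparison cannot see what switching under MBC does. The documents do not support that, for five reasons.

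- The hypothesis concerns side-effect burden and dropout. FIBSER measures burden and discontinuation is compared between arms. Joining symptoms on the checklist affects neither, nor does it affect the three single items.
- No side-effect profile is given for either drug. A different mechanism does not show that a switch turns diarrhea into constipation, or does the like for the other pairs, two of which are not opposites. Exact cancellation is an assumed worst case.
- Present/absent scoring is itself assumed. SAP 3.2 allows t-tests and Mann-Whitney tests as well as chi-square tests, and a graded item might register some change.
- The protocol allows one drug change in its general procedure, so only a difference in switching between the arms would matter.
- SAP 3.2 specifies no comparison item by item.

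All five stand, and they limit the point to symptom-level reporting. They do not remove it. FIBSER, as described, rates frequency, intensity and burden without naming a symptom. Discontinuation does not name one either, and the SAP keeps only the all-cause version where the protocol also had specific-cause discontinuation. The silence on scoring is part of the gap.

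A further fair objection is timing. SAP 3.1 reports in the past tense that no interim analyses were done, which suggests that data collection was well advanced. Reprinting the form may no longer be possible, so a fallback is needed.

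**Conclusion.** The point holds in a limited form. Half of the checklist items (3 of 6) combine two symptoms, and the documents do not say that the halves are kept apart. Under present/absent scoring, differences between arms in those six symptoms can be diluted or, at worst, cancelled, and no other named measure would show which symptom changed.

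In the assumed example, power falls from 58% for the symptom recorded alone to between 51% and 5% for the joint item, depending on the share traded. These figures rest on assumed rates, on symptoms that do not co-occur, and on binary scoring. They show how joining acts and do not predict what this trial will find. Equal rates on a joint item should not be read as equal rates of each symptom. The weakness is minor and cheap to remove.

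**What to change.** - **Form.** Record nine single symptoms: dry mouth, diarrhea, constipation, dizziness, drowsiness, loss of appetite, nausea, headache, excessive sweating. State how each is scored.
- **SAP 3.2.** Tabulate each symptom by arm descriptively. Derive the six joint items as present when either half is present, so that comparison with the replicated trial is kept.
- **Fallback.** If the forms are already completed with joint items only, state the scoring that was used, report the three joined items as composites, and say that equal rates on a composite do not show equal rates of its parts. If the halves were in fact captured, tabulate them.

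Cost: three more tick boxes and nine descriptive rows instead of six. Formal tests on all nine would add multiplicity with limited power at 60 per arm, which is why the table should be descriptive.
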